## Discussion

The majority of patients with CHD do not access existing cardiac rehabilitation programs. Testing of alternative models of secondary prevention will potentially provide beneficial programs for more high risk patients following ACS.

We have presented the rationale and design for a randomised controlled trial testing a modular approach to the secondary prevention of CHD. The study is also designed to compare outcomes to benchmarks set by patients participating in standard cardiac rehabilitation. The primary outcomes will be the magnitude of CHD modifiable risk factors and secondary outcomes will be relative CHD risk and knowledge of these factors.

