### Outcome measures

Assessments will be conducted in the hospital consulting rooms or in the participant's home, if they are unable to travel to the hospital. Demographic, subjective and objective information will be obtained during face-to-face assessments at baseline, three and 12 months. Information will include past history, nature of ACS, family history, age, medications and dose, presence of other cardiovascular disease and the nature and date of any revascularisation. In addition, contact details for each participant, their general practitioner and their cardiologist will be documented.

At three and 12 month follow-up, all baseline measures will be repeated during face-to-face assessments by a researcher blinded to group allocation. Additional collected information will include – details of unplanned hospital admissions, medications and doses along with details of any health interventions undertaken by the participant pertaining to their heart health, such as visits to the GP and attendance at community programs. For participants in the standard rehabilitation group, details of participation in the cardiac rehabilitation program will also be recorded such as duration and attendance at exercise and education sessions.

Modifiable risk factors to be measured are serum cholesterol, BP, smoking status, physical activity, overweight and depression. Lipids and substrates will be measured on a fasting blood sample within two weeks of assessment date. Participants will be referred to local pathology clinics by their primary care doctor and will visit the clinics by their own arrangement. Blood samples will be analysed for determination of total cholesterol (TC), low density lipoprotein cholesterol (LDL-C), high density lipoprotein cholesterol (HDL-C) and triglycerides (TG). Repeat blood tests will be carried out at the same pathology clinic wherever possible.

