#### Modular group

Participants randomly allocated to the modular group will manage their heart health by participation in modular guided self-choice management of heart disease. That is, participants will participate in risk factor modules of their choice, with the exception of the mandatory blood cholesterol module, strive to achieve mutually-agreed goals and make choices about risk factor reduction interventions based on their own circumstances. Following baseline assessment, the consultation will be extended by approximately 30 minutes for selection of modules, goal setting and shared decision making about risk factor interventions.

The risk factor modules consist of cholesterol-lowering, BP management, smoking cessation and physical activity. All participants will participate in the cholesterol-lowering module and where applicable, participants can also choose up to two other modules depending on their individual risk factor assessment and personal preference. Therefore, all participants will participate in a minimum of one risk factor module and a maximum of three modules at any one time.

The mandatory cholesterol-lowering module involves pharmacological intervention in consultation with the primary care doctor as well as education and empowerment through information and support about individual and nationally recommended cholesterol levels. The three optional modules involve choice of intervention including; following medical advice; participating in a structured program (individual or group); participating in a home program; or self-help. All risk factor modules will be resourced and delivered separately among the primary care doctor, the local area health service, the local community and the participant. Participants in the modular group will receive a resource package including appropriate information leaflets which contain guidelines and information about the module and contact information for community heart health programs. The leaflets have been developed and pilot tested, for validity, by health professionals and consumers.

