### Sample size

Participant numbers required for each group have been calculated to detect a 0.5 mmol/L reduction in TC with 80% power. The LIPID study of 9014 subjects with CHD reported a mean TC of 5.6 (± 0.7) mmol/L [40] and it has been assumed that a clinically significant change in TC would be 0.5 mmol/L. Therefore, to achieve power of 80% to detect a change of 0.5 of a SD unit, using a two-tailed test with an alpha level of 0.05 and allow for 10% loss to follow-up, it was calculated that 72 participants per group will be recruited.

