### Data analysis

Data will be analysed by intention-to-treat using SPSS for Windows (Version 12.01) and will be presented as mean and standard error of the mean or proportions. Differences in outcome measures, between and within groups, will be compared using repeated measures ANOVAs for continuous variables and either χ^2 ^tests or Fishers exact tests, as appropriate, for proportions of categorical variables. Two tailed p values of < 0.05 will be considered significant.

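### The modifiable risk factors are all unranked primary outcomes tested at 0.05, but the trial is sized on one total cholesterol test, so a 5% error rate does not cover the primary claim

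*Protocol article*

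**What the plan says.** The outcome hierarchy appears only in the Discussion of the protocol article: "The primary outcomes will be the magnitude of CHD modifiable risk factors". Relative risk and knowledge are secondary. Outcome measures gives the list: "Modifiable risk factors to be measured are serum cholesterol, BP, smoking status, physical activity, overweight and depression". That is six factors, and some have more than one measure. The blood sample, for example, is for "determination of total cholesterol (TC), low density lipoprotein cholesterol (LDL-C), high density lipoprotein cholesterol (HDL-C) and triglycerides (TG"). On timing, "At three and 12 month follow-up, all baseline measures will be repeated during face-to-face assessments"; neither visit is named as the primary one.

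Data analysis gives the method, "Differences in outcome measures, between and within groups, will be compared using repeated measures ANOVAs for continuous variables", with chi-square or Fisher tests for categorical variables, and the threshold, "Two tailed p values of < 0.05 will be considered significant".

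Sample size describes one test only. Numbers were "calculated to detect a 0.5 mmol/L reduction in TC with 80% power", using a two-sided alpha of 0.05, a standardised difference of 0.5 SD and 10% loss to follow-up, which gives 72 per group.

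**The concern.** Sample size and the Discussion describe two different primary analyses. The first is one test of total cholesterol at 5%. The second is six co-equal tests with the same 5% threshold available to each. The outcome that the trial was sized for has no special standing in the second.

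The main conclusion is at stake. The nominal 5% applies to any single test, but not to a claim that the programme improved a primary outcome when any of six could supply it. The article gives no rule for how many factors, or which, must improve.

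**Working it through.** **Inputs.** Six factors and follow-up at 3 and 12 months (Outcome measures); two-sided 0.05 (Data analysis); 0.5 SD, 80% power, 10% loss, 72 per group (Sample size). The documents give no correlations between outcomes or between times, so these are assumed and varied. Only modular versus conventional is counted.

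**1. The plan's own figure.** A two-sample t-test at 0.5 SD, two-sided 0.05 and 80% power needs 63.8, so 64 evaluable per group. Then 64 / 0.90 = 71.1, rounded up to 72. The stated figure reproduces exactly, as one test at the full alpha.

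**2. One test per factor.** The chance of at least one false positive among k independent tests is 1 − 0.95^k.
- k = 6: 1 − 0.95^6 = 26.5%.
- With correlated outcomes (simulated multivariate normal z statistics, rejecting when |z| > 1.96): about 25% at correlation 0.2, 24% at 0.3 and 21% at 0.5.

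**3. Closest reading of Data analysis.** Repeated measures ANOVA can test a continuous outcome once across visits. Smoking status is categorical, and chi-square or Fisher tests do not combine visits. Five single tests plus smoking at two visits makes seven.
- Independent: 1 − 0.95^7 = 30.2%.
- With 0.6 assumed between the two smoking tests: about 28% at between-outcome correlation 0.2, and 23-24% at 0.5.

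Steps 2 and 3 together give about 21-30%.

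**4. Every factor tested separately at both visits.**
- Twelve independent tests: 1 − 0.95^12 = 46.0%.
- Correlation 0.2 between outcomes and 0.6 between times: about 41%.
- Correlation 0.5 between outcomes and 0.6 between times: about 34%. If the two times correlate at 0.8 instead, this falls to about 31%.

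**5. Could an alpha split repair it at the planned size?** Bonferroni over six gives 0.05 / 6 = 0.0083. At 0.5 SD and 80% power this needs 98.6, so 99 evaluable per group, and 99 / 0.90 = 110 recruited. With the planned 64 evaluable, power is 56%.

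**The case against.** **A success rule is being inferred.** A reader might infer that the plan declares the trial positive if any one factor reaches 0.05. It does not say so; Data analysis states a general threshold. This objection stands, and the percentages are conditional on that use of the results. But no other rule is stated, so the reading is open.

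**The highest figures do not follow from the stated analysis.** A reader might also infer an error rate of 40% or more from six factors at two visits. That needs separate tests of every factor at each visit, whereas the repeated measures ANOVA can give one test per continuous outcome. This stands, so 21-30% is the figure to attach to the plan as written.

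**The analysis plan may handle multiplicity.** It is not shown, and a condensed article may leave the adjustment to it, so a missing adjustment is not the complaint. What remains is the mismatch within the article. At 0.5 SD, an alpha split made elsewhere would break the stated power.

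**That loss of power depends on 0.5 SD.** Sample size also cites 0.5 mmol/L with an SD of 0.7, which is 0.5 / 0.7 = 0.71 SD. On that basis 64 evaluable per group would have about 91% power for total cholesterol even at 0.0083. This is fair, but it is not the effect size used for the 72, and no effect size is given for the other five factors.

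**Untargeted primaries.** A reader might infer a further fault because "The risk factor modules consist of cholesterol-lowering, BP management, smoking cessation and physical activity", with none for overweight or depression. The documents do not support this. The Modular group section offers participants identified as depressed a psychologist appointment, physical activity may affect weight, and the objective is the overall risk profile. It also has no bearing on the error rate.

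**Conclusion.** The point holds. The plural, unranked primaries, the absence of a primary time, the single 0.05 threshold and the sizing on one cholesterol test are all on the page and need no assumption. The stated 5% error and 80% power cannot both be kept for the declared primary set at the 0.5 SD used.

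The false-positive chance of about 21-30% assumes three things: no true effect on any factor, a claim of success on any one factor, and between-outcome correlations of 0 to 0.5. The 34-46% range also needs separate tests at both visits, with between-time correlation up to 0.6. The extra lipid measures, within-group tests and comparisons with the reference group are not counted; treating any of them as primary would add to these figures.

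**What to change.** Make the Discussion agree with Sample size. Name total cholesterol, modular versus conventional, as the single primary outcome, tested at two-sided 0.05 at one pre-specified time. Twelve months fits the one-year follow-up in Design, but this is an inference: goals and coaching are concentrated in the first three months, so the sponsor should state its choice. Make the other five risk factors and the other time point secondary, either with Holm adjustment or reported as estimates with 95% confidence intervals.

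If one cholesterol value seems too narrow for the objective, the number of modifiable risk factors per participant, already defined in Outcome measures, is another possible single primary. It would need its own sample size calculation, which total cholesterol does not.

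The cost is a wording change, made before outcome data by group are seen, with no added participants. The downside is that an isolated effect on another risk factor could no longer be claimed as a primary success.
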